### Eligibility

#### Site eligibility

The UC programme at a site must meet the stated criteria, have a sufficient referral rate (or waiting list size) to be able to recruit patients within the study period, and have a multidisciplinary SWMS team with the capacity to run the PROGROUP sessions.

#### Inclusion criteria

Participants must satisfy all the following:

Registered with the SWMS (in the UK).A BMI≥37.5 kg/m^2^ or BMI≥32.5 kg/m^2^ with at least one significant comorbidity* at the point of consent for individuals with a South Asian, Chinese, other Asian, Middle Eastern, Black African or African-Caribbean family background. A BMI≥40 kg/m^2^ or BMI≥35 kg/m^2^ with at least one significant comorbidity* at the point of consent for all other individuals.Age≥18 years.Willing to be randomised to either PROGROUP or UC.Willing to have weight measured on at least three occasions: baseline and 6 months (and 12 months for those recruited before the final follow-up was changed to 6 months).Willing to provide blood samples and blood pressure readings on three occasions: baseline and 6 months (and 12 months for those recruited before the final follow-up was changed to 6 months).Considered suitable for group-based care.Have capacity to consent.

* Type 2 diabetes, hypertension, dyslipidaemia, cardiovascular disease, osteoarthritis, obstructive sleep apnoea and ‘other’. Suitability of ‘other’ will be determined on a case-by-case basis.

#### Exclusion criteria

Participants meeting any of the following will be excluded:

Already undergone bariatric surgery.Are scheduled, or have made their own plans, to undergo bariatric surgery during the trial.Currently taking the following pharmacotherapy for the indication of weight loss: Semaglutide, Tirzepatide, Liraglutide, Orlistat or any off-licence weight-reducing pharmacotherapy such as the stimulant appetite suppressants phentermine and diethylpropion. Commencing these medications from post-randomisation is allowable. (For those recruited prior to implementing the adjusted programme of work, starting these medications within 6 months post randomisation was not allowable.)Currently engaged in any other weight management trial.Unwilling or unable to attend the SWMS for intervention/UC appointments.Intending to relocate outside the geographical region during the trial period.Participants who have significant difficulties in adequate understanding of English, or a sensory impairment, such that they are unable to sufficiently understand/access the trial documentation or engage in intervention/UC appointments, in the absence of a local provision of translated materials or communication aids.

### Collection of data

Data will be entered by site staff or participants, as applicable, to an electronic data capture system built and maintained by the CTU, comprising a bespoke web-based database and REDCap Community. See table 1.

**Table 1 T1:** Study schedule

		Pre-baseline	Baseline	Randomisation	Post-randomisation		
Time point			*t_0_*		3 months (coincides with intervention mid-point)	6 months (−2 weeks to +4 weeks window) t_*1*_	12 months* (−2 weeks to +4 weeks window) *t*_*2*_
Enrolment:							
Eligibility screen		X	X				
Informed consent			X				
Randomisation				X			
Interventions:							
Control group:	Usual care (dotted line)						
Intervention group	Usual care (dotted line) PROGROUP (solid line)						
Assessments:							
Demographics			X				
Weight (kg) within 6 weeks prior to randomisation			X			X	X
Height (cm) within 6 weeks prior to randomisation			X				
HbA1c (mmol/mol) at or within 1 month prior to baseline visit (eg, from medical records).			X			X	X
Lipid profile (mmol/L) at or within 1 month prior to baseline visit (eg, from medical records).			X			X	X
Systolic blood pressure (mm Hg)			X			X	X
Co-morbidities			X			X	X
Medications†			X			X	X
Adult Eating Behaviour Questionnaire (AEQB)‡			X			X	X
Alcohol use (Audit-C)‡			X			X	X
International Physical Activity Questionnaire‡ (IPAQ) short form‡			X			X	X
ICEpopCAPability measure for Adults (ICECAP-A)‡			X			X	X
Patient Health Questionnaire-4 (PHQ-4)‡			X			X	X
Self esteem and life satisfaction measure(s)‡			X			X	X
EQ-5D-5L questionnaire‡			X			X	X
Social identification measure‡			X		X	X	X
Loneliness measure‡			X			X	X
Resource use questionnaire‡			X		X (weight loss medication and surgical procedures only)	X	X
Participant travel costs (for intervention costing)‡					X	X	
Safety monitoring:							
Adverse event reporting							

* Applies only to participants randomised prior to implementation of the adjusted programme of work.

† Self-reported by participants and also reported by site staff with access to medical records.

‡ Self-reported by participants.

#### Baseline measurements

For eligible and consented participants, site staff will record baseline clinical measures: height, weight, blood lipid profile (total cholesterol, HDL cholesterol, triglycerides), systolic blood pressure and glycaemia measurement (HbA1c). Informed consent will be documented on a study-specific consent form (see online supplemental material 1).

Due to the group-based nature of the PROGROUP treatment, sites are required to recruit participants as a cohort (of 24–36 participants) prior to randomisation of that cohort.

To minimise the gap between baseline clinical measurements and randomisation, self-reported baseline assessment questionnaires will only be issued to participants after a full cohort has been recruited. The decision to declare a cohort complete will be made by the Co-Chief Investigators in consultation with the Trial Management Group.

The time from eligibility assessment (including weight measurement for derivation of BMI) to randomisation must be less than 6 weeks. In the event that this interval exceeds 6 weeks, baseline weight will be re-measured prior to proceeding with randomisation. Other clinical baseline measures will not be repeated since these are considered unlikely to change in this interval.

#### Follow-up assessments

Participants will attend a face-to-face clinic where, using a study-specific electronic case report form (eCRF), a blinded outcome assessor will record participant weight, HbA1c, lipid profile and blood pressure, and any use of OMM or bariatric surgery undertaken. Alternative arrangements for measurement of weight might be appropriate in exceptional circumstances and on a case-by-case basis, for example, weight measured at the participant’s home by trained staff using calibrated clinic weighing scales.

Separately, participants will complete the self-reported measures.

### Withdrawal

The risk of harm to participants caused by treatment in either trial arm is very low; however, there is a potential risk of participants requesting to withdraw from the PROGROUP arm for psychological reasons (eg, being uncomfortable with the group-based format of the PROGROUP arm, as observed in the feasibility RCT). Participants may choose to withdraw at any time.

Intervention facilitators may also choose, at their discretion, to withdraw participants from the PROGROUP programme. Grounds for withdrawing participants from the PROGROUP programme may include, for example, disruptive behaviour or wilful non-engagement.

Withdrawal from the PROGROUP programme, and the reason if provided, will be clearly documented in the participant’s clinical records reported using a study-specific eCRF.

All participants withdrawn from PROGROUP or UC will be encouraged to continue with follow-up visits and assessments as per the trial protocol.

Data collected prior to withdrawal from follow-up will be included in the study analysis. Participants who withdraw after their cohort has been randomised will not be replaced with new participants, due to the nature of the trial intervention.

### Adverse events

The likelihood of participants being harmed by either the PROGROUP intervention or any of the trial procedures is very low. As such, the collection and reporting of events in the PROGROUP trial is restricted to only those events which are deemed to be serious adverse events (SAEs).

The primary means of detecting SAEs will be at the follow-up clinic visits and the intervention sessions. At each contact point, participants will be asked to describe any adverse events (AEs) they have experienced.

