**Methods and analysis:**

The RCT will be conducted in SWMS, alongside an implementation study in primary care. The RCT will recruit cohorts of 30 participants to be randomised 1:1 within-cohort to PROGROUP (intervention) or usual care (control). The implementation arm will recruit cohorts of 15 to PROGROUP. The primary objectives for the study are to undertake a process evaluation and economic evaluation of PROGROUP in the RCT and to assess its implementation in primary care. Baseline data and outcome differences at 6 months will be analysed. These will include weight, other clinical measures and patient-reported outcomes, including social and life-satisfaction measures.

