### Treatments

#### Usual care

UC will be an existing programme consistent with the principles of the National Institute for Health and Care Research (NICE) guidelines CG189^49^ and NG246.^50^ It is expected that there will be some variation in the structure and delivery of UC, reflecting normal practice nationally.^51^ Group education activities that are sometimes used in UC (eg, introduction meetings, healthy eating education, activity sessions, bariatric education) will be permitted. However, dedicated group activities beyond provision of didactic educational information, such as group discussions and activities including group-based problem solving and consensus forming, which is the defining feature of the PROGROUP intervention and is not present in the great majority of SWMS UC interventions, are not permitted in this study.

In this study, for a given cohort of participants, the UC programme will commence at the same time as the PROGROUP programme.

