#### PROGROUP

PROGROUP is a manualised intervention and will be provided to participants in accordance with the manual by purposely trained facilitators from a multidisciplinary team (typically, nurses, dieticians or physiotherapists) at each site.

Participants will be asked to make every reasonable effort to adhere to the intervention programme schedule. The importance of engagement with all trial activity will be emphasised to all participants in both arms the PROGROUP intervention specifically via a study-specific charter.

The PROGROUP intervention consists of 15 sessions over 5 months:

Weeks 1–2: Each participant will attend an initial one-to-one meeting with a facilitator, to review medical history, motivations and preparations for joining the group.Weeks 3–10: Participants will attend eight consecutive weekly group sessions, to teach and build on behavioural skills.Weeks 11–12: Each participant will attend an interim one-to-one meeting with the facilitator to review progress.Weeks 14–18: Participants will attend three consecutive fortnightly group sessions focusing on behavioural maintenance.Weeks 19–20: Final one-to-one meeting with the facilitator, for clinical review to develop plans for individualised continuation of programme learning.Week 22: Final group session to conclude intervention and prepare for self-directed implementation of programme learning.

A PROGROUP group will consist of approximately 15 participants (anticipated range of 12–18 participants). Each PROGROUP group session will be face-to-face and will take 2 hours inclusive of breaks. Group sessions will be delivered face-to-face, although for those recruited after the final follow-up was changed to 6 months, sites may opt to deliver some/all of the group sessions 4–8 remotely. These sessions will be audio recorded to be analysed using inductive thematic analysis, with video recordings obtained from a sample of sites. The one-to-one meetings will be 1 hour long and can be held either face-to-face or remotely (eg, telephone, video call) to offer flexibility to both participants and facilitators.

While there is no established ‘minimum dose’ for PROGROUP, all participants (in both arms) will be asked to make every reasonable effort to adhere to their programme schedule.

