### Monitoring

The PROGROUP Programme Steering Committee has formally agreed to adopt the role of TSC for this trial. The TSC will meet every 6–7 months in accordance with an agreed set of terms of reference to review the progress of the trial and any SAEs and will report to the Sponsor. A Data Monitoring and Ethics Committee will not be convened for this trial, which is considered to pose low risk of harm to participants. The TMG meets monthly to review trial progress and to ensure appropriate management of the trial, in accordance with the terms of reference for the group.

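### The named SAE detection routes give PROGROUP up to 15 enquiry points with no stated usual-care counterpart, so by-arm SAE counts may differ through ascertainment alone

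*Protocol article*

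**What the plan says.** The Adverse events section of the protocol article limits event collection and reporting: it is "restricted to only those events which are deemed to be serious adverse events (SAEs". It then names two routes: "The primary means of detecting SAEs will be at the follow-up clinic visits and the intervention sessions". The next sentence adds: "At each contact point, participants will be asked to describe any adverse events (AEs) they have experienced". It does not define a contact point.

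Other sections bear on how this is read:

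- The abstract (Methods and analysis) labels the arms: participants are "to be randomised 1:1 within-cohort to PROGROUP (intervention) or usual care (control".
- The trial's Exclusion criteria name the two kinds of contact side by side: "Unwilling or unable to attend the SWMS for intervention/UC appointments".
- The PROGROUP section sets the contact schedule in one arm: "The PROGROUP intervention consists of 15 sessions over 5 months".
- The Usual care section sets none for the other: "It is expected that there will be some variation in the structure and delivery of UC, reflecting normal practice nationally".
- Under Changes to the definitive trial protocol and in Table 1, clinic follow-up is one visit at 6 months. Cohorts randomised before the adjusted plan also have a 12-month visit. The 3-month items in Table 1 are self-reported.
- The Monitoring section gives SAE review to the steering committee and states: "A Data Monitoring and Ethics Committee will not be convened for this trial". The Blinding section lets that committee see unblinded data on request.

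**The concern.** If one arm is asked about events at every session and the other mainly at a clinic visit, the arm asked more often will record more events at the same true risk. Two mechanisms act. A PROGROUP participant who later misses the 6-month clinic may already have reported an event at a session. An event forgotten by 6 months may have been reported soon after it happened. Both push recorded SAEs upwards in PROGROUP. The session enquiries are also made where allocation is known, whereas follow-up assessors are blinded.

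SAEs are the only adverse event data the trial collects, so the asymmetry reaches all of them. The steering committee reviews them without a separate data monitoring committee. If it looks at counts by arm, it could read an ascertainment difference as a harm of the group programme.

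**Working it through.** **1. Which sessions are meant.** The abstract attaches *intervention* to PROGROUP and *control* to usual care. The trial's exclusion criteria list intervention and usual-care appointments as separate things. The implementation study's exclusion criteria, where there is no usual-care arm, refer to intervention sessions alone. Table 1 does place usual care under a general heading for interventions, but that is a schedule heading and does not turn usual-care appointments into intervention sessions. The named route is therefore PROGROUP sessions.

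**2. Session count.** From the PROGROUP section: 1 initial one-to-one + 8 weekly group + 1 interim one-to-one + 3 fortnightly group + 1 final one-to-one + 1 final group = 15. This reproduces the stated figure.

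**3. Named enquiry points per participant, at full attendance.**

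| | PROGROUP | Usual care |
|---|---|---|
| Adjusted plan | 15 + 1 = 16 | 1 |
| Cohorts with a 12-month visit | 15 + 2 = 17 | 2 |

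**4. Effect on counts when true risk is equal.** This is a simulation over the first 6 months. The only input from the document is the 30% dropout in the Sample size section, applied here to both arms as non-attendance at 6 months. The rest is assumed:

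- Event times are uniform over 26 weeks.
- Among those who miss the 6-month visit, the time of leaving is uniform over the same period.
- Session attendance is 70% until a participant leaves.
- An event is always reported at the next session attended.
- Recall *r* applies at the 6-month clinic.
- Usual-care appointments involve no enquiry.

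Usual care: captured share = *a* × *r*, where *a* is attendance at 6 months. With *a* = 0.70 and *r* = 1, this is 0.70.

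PROGROUP: an event is captured if it is reported at the clinic or at any attended session after it occurs. With *a* = 0.70 and *r* = 1, all events in the 70% who attend are captured. The simulated total is 0.83, so sessions recover (0.83 − 0.70) / 0.30 = 0.43 of events in the 30% who do not attend.

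Apparent ratio = 0.83 / 0.70 = 1.19.

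| 6-month attendance | Recall 100% | Recall 80% | Recall 60% |
|---|---|---|---|
| 90% | 1.05 | 1.26 | 1.62 |
| 80% | 1.11 | 1.34 | 1.72 |
| 70% | 1.19 | 1.44 | 1.86 |
| 60% | 1.29 | 1.57 | 2.03 |

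The range is 1.05 to 2.03, with session attendance held at 70%.

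**5. What that means in events.** The Sample size section expects 120–140 participants for the cost-consequence analysis, about 60–70 per arm. SAE risk is not given. At an assumed 2–10% the true number per arm is 60 × 0.02 = 1.2 to 70 × 0.10 = 7. For a middle case of 65 per arm and 5% risk, true events are 65 × 0.05 = 3.25 per arm. Captured events are 3.25 × 0.83 = 2.7 in PROGROUP and 3.25 × 0.70 = 2.3 in usual care, a gap of about 0.4. At the extreme (7 true events, 60% attendance, 60% recall, captured shares 0.728 and 0.36) the counts are 5.1 and 2.5, a gap of about 2.6.

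**The case against.** The strongest reply is that the sentence on contact points is not limited to an arm. Usual-care participants attend appointments in a programme that starts alongside PROGROUP. If those appointments count, the 16 to 1 contrast falls away. This stands as a real ambiguity, but it does not settle the matter: the sentence follows directly on a list with no usual-care contact, and usual-care contact varies by site, so the frequency of asking would still be unequal and unknown.

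The routes are also called primary, not exclusive, and this is an article that condenses a fuller protocol where further reporting routes may be set out. The adverse event row in Table 1 has no entries in the text available here, and its marking may have been lost in extraction, so nothing can be drawn from it. These points stand. A reader might infer that usual-care SAEs in people who miss follow-up go wholly undetected, but the document does not support that. PROGROUP participants who stop attending are likewise missed after their last session.

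Finally, no between-arm SAE analysis is described. A reader might infer that a planned safety comparison is biased and certain to show an excess. The document supports only a risk to any by-arm tabulation or committee review that is made. A larger ratio is also tempting: usual-care detection of 0.70 × 0.70 = 0.49 to 0.70 × 0.90 = 0.63 against an assumed 0.90 in PROGROUP gives 0.90 / 0.63 = 1.4 to 0.90 / 0.49 = 1.8. That applies the 30% non-attendance to usual care only, whereas the protocol's allowance is not specific to an arm.

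**Conclusion.** The point holds in a limited form. As written, the protocol names a frequent SAE detection route for PROGROUP and no counterpart for usual care, so ascertainment is potentially differential and its direction is towards more recorded SAEs in PROGROUP. With both arms treated alike, the illustrative ratio is about 1.19 at 30% non-attendance and perfect recall, and about 1.05 to 2.03 over the assumed range. Clinic attendance other than 70%, session attendance, recall and SAE risk are all assumptions. The figures also assume that usual-care appointments are not contact points; if they are, the distortion shrinks. SAEs are likely to be well remembered, which favours the lower values. In absolute terms the gap is probably under one event per arm in the middle case, so chance would matter at least as much. It is still worth correcting, because these are the only harms data collected and the correction is cheap.

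**What to change.** Amend the Adverse events section so that SAE enquiry uses the same schedule and sources in both arms, and state whether usual-care appointments are contact points. The common sources could be the 6-month clinic visit, the hospital items of the resource-use questionnaire, and the access to medical records that site staff already use when reporting medications. The article describes the last two for both arms but does not link them to SAE reporting.

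Base any between-arm SAE summary, including one shown to the steering committee, on those common sources only. List SAEs detected only at PROGROUP sessions separately, without comparing them between arms. Session enquiry itself can continue.

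The cost is a few sentences in the protocol and analysis plan and slightly more site and tabulation work. The comparative table would contain fewer SAEs, but the separate listing means none goes unreported.

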### Sample size and statistical methods

The original definitive trial sample size calculation was informed by previous literature^52–57^ and the PROGROUP feasibility RCT. The recruitment target after changing the primary endpoint to 6 months was 780 participants, from~26 cohorts across eight recruiting sites. This target was calculated based on detecting the pre-specified between-group mean difference in weight loss of 3 kg, with 90% power and 5% two-sided significance level, with assumed SD of 7 kg, mean cluster size in each treatment arm (at 6 months) of 10 participants (with cluster size variability of 9), intra-cluster correlation coefficient of 0.025 in UC and 0.2 in PROGROUP, and allowing for 30% dropout rate.

Given that the RCT will be underpowered to detect the pre-specified between-arm difference in weight change under the original sample size assumptions, statistical analysis of the RCT will focus on a descriptive approach.

Descriptive statistics of participants’ demographic and baseline characteristics will be presented by allocated groups and overall. Continuous data will be reported with means and SD if they appear normally distributed, otherwise the median and inter-quartile range will be used. For categorical data, frequency and proportions will be presented.

The primary descriptive analysis of all outcomes will follow an intention-to-treat approach. For the primary estimand, the analysis will use the treatment policy strategy to handle the key intercurrent events of intervention discontinuation and initiation of weight loss medication. A mixed effects model will be fitted for the primary outcome, including participants with weight measured at baseline and at 6 months post-randomisation, allowing for differential clustering between the control and intervention groups, and adjusting for relevant individual covariates, site, and baseline weight. Model parameter estimates and CIs will be presented; however no formal hypothesis tests will be conducted. Missing data will not be imputed.

The number of participants achieving a clinically meaningful weight loss of ≥5% and ≥10% baseline body weight at 6 months post-randomisation will be reported as the number and proportion meeting this threshold by trial allocation arm and overall.

Sensitivity analyses will use subgroups of the full dataset that exclude participants that

Discontinued from the treatment.Used OMM during the trial period.Underwent bariatric surgery.

If any sites offer group-based care as part of their UC, a subgroup analysis will be undertaken where the effect of UC type will be explored.

Full details of the planned analyses will be described in the statistical analysis plan (SAP), which will be finalised prior to database lock. Once finalised, the SAP will be uploaded to the ISRCTN registry along with the trial protocol.

A formal sample size calculation has not been conducted for the cost consequence analysis. For this analysis, we estimate that 120–140 participants across six cohorts is feasible, based on predictions for recruitment of sites and participant recruitment rate.

